**Fig. 3 Fig3:**
[figure not shown]
Flowchart of procedures with timelines of (**a**) healthcare professionals and (**b**) patients and informal caregivers. Abbreviations HCP: health care professionals; iT0: professional timeline at baseline (pre-implementation); iT3: 3 months after inclusion of first included patient (initial implementation); iT12: 12 months after training (intervention regions) or inclusion of first patient (control regions) (late implementation); T0: patient timeline at baseline; T3: patient timeline at 3 months; T6: patient timeline at 6 months; R: retrospectively

### Effect evaluation

An overview of the data collection process, detailing the timing of data collection and the outcome measures and instruments used, is provided in Table 2.

**Table 2 Tab2:** Data collection schedule and measurement instruments for patients, informal caregivers and healthcare professionals

	Measurement instrument				
**Patient**		**T0**	**T3**	**T6**	**R**
Baseline characteristics	Questionnaire on demographic characteristics and case report form on disease severity	x			
Quality of life (primary outcome)	Functional Assessment of Chronic Illness Therapy-Palliative care (FACIT-Pal) scale [35]	x	x	x	
Spiritual well-being	Functional Assessment of Chronic Illness Therapy - Spiritual Well-Being (FACIT-Sp-12) scale [36]	x	x	x	
Anxiety and depression	Hospital Anxiety and Depression Scale (HADS) [37]	x	x	x	
Disease-specific health-related quality of life	Clinical COPD Questionnaire (CCQ)	x	x	x	
Satisfaction with care	Single item question on satisfaction with provided care, self-rated on a numeric rating scale (NRS) from 0 to 10	x		x	
Unplanned healthcare use	Medical record assessment on number of ED visits (without admission), hospital admission (number and number of days), ICU admission (number and number of days), in the 12 months pre-enrollment up to 12 months after enrollment				x
Date and place of death, place of care in last week of life if applicable	Medical record assessment (and contact with general practitioner if needed)				x
Dose received	Questionnaire on received core elements, based on three validated questionnaires [38–40]	x		x	
	Medical record assessment on core elements				x
Experiences and acceptability	Semi-structured interviews		x^a^		
**Informal caregiver**		**T0**	**T3**	**T6**	
Baseline characteristics	Questionnaire on demographic characteristics	x			
Caregiver burden	Caregiver Reaction Assessment (CRA) scale [41]	x	x	x	
Satisfaction with care	Single item question on satisfaction with provided care to the patient, self-rated on a NRS from 0 to 10	x		x	
Experiences and acceptability	Semi-structured interviews		x^a^		
**Health care professional**		**iT0**	**iT3**	**iT12**	
Self-efficacy	End-of-life professional caregiver survey (EPCS) [42]	x	x	x	
Role identity	Developed five-item question on role identity based on MIDI questionnaire [43]	x	x	x	
Satisfaction with care	Single item question on satisfaction with provided palliative care to patients with COPD, self-rated on a 5-point Likert scale	x	x	x	
Dose delivered	Self-reported provision of delivered core elements	x	x	x	
Experiences, acceptability and determinants to implementation	Semi-structured interviews			x	

*T0* patient timeline at baseline; *T3* patient timeline at 3 months; *T6* patient timeline at 6 months; *R* retrospectively; *iT0* pre-implementation (professional timeline at baseline); *iT3* initial implementation (3 months after inclusion of first patient); iT12 = late implementation (12 months after training (intervention regions) or inclusion of first patient (control regions))

^a^ Interviews will be held with a purposeful sample of patients and informal caregivers between 3 and 6 months after inclusion

### Primary effect outcome

The primary outcome is quality of life as measured with the Functional Assessment of Chronic Illness Therapy-Palliative care (FACIT-Pal) scale. This scale is a validated 46-item questionnaire comprising of a general part with four subscales on physical well-being, social/family well-being, emotional well-being and functional well-being, respectively, and a specific part regarding palliative care [35]. The total score ranges from 0 to 184; a higher score indicates a better quality of life. Since a Dutch version of the FACIT-Pal questionnaire was not yet available, the items of the palliative care subscale were first translated in collaboration with the FACIT organization, following the FACIT translation/linguistic validation methodology [44]. After a comprehensive forward-backwards translation process, the concept version of the translated FACIT-Pal questionnaire was tested through retrospective and cognitive interviews in ten patients: six with very severe COPD, three with lung cancer and one with both COPD and lung cancer. Recruitment of these patients took place in a pulmonology ward, outpatient clinic, as well as a pulmonary rehabilitation center.

### Secondary effect outcomes

Secondary effect outcomes will be spiritual well-being, disease-specific health-related quality of life, unplanned healthcare use, date and place of death if applicable, informal caregiver burden and professionals’ self-efficacy and role identity with providing palliative care and discussing end-of-life. Satisfaction with care will be assessed at the patient, informal caregiver and professional level. The measurement instruments to be used are detailed in Table 2.

### Baseline measures

Demographic characteristics of patients that will be collected are sex, age, ethnicity (western and non-western), marital status, living situation, an education level (high, medium, low), smoking status, pack years. Also, characteristics of disease severity (long term oxygen use, home non-invasive ventilation use, previous ICU admissions, previous mechanical ventilation and opioid use before hospital admission) will be collected. Demographic characteristics of informal caregivers that will be collected are sex, age, education level (high, medium, low) and current job. Demographic characteristics of professionals that will be collected are function, years of experience, palliative care experience and education.

### Sample size calculation

Our primary outcome measure is quality of life measured with the FACIT-Pal. The clinically relevant difference is suggested to be between 4 to 6% of a measure’s overall score for the Functional Assessment of Cancer Therapy (FACT) scores, including the FACIT-Pal [45]. A previous systematic review on palliative care interventions used the 5% midrange bound, which equals 9 points on the FACIT-Pal [46]. Assuming a standard deviation of 25 [47], at least 121 patients per group are required to obtain a power of 80% (two-sided t-test, alpha = 0.05). To adjust for the clustering at hospital level (a previous study found an ICC = 0.01 [32]) and to allow for an additional loss to follow up of 10% a total of 347 patients are needed (44 patients per region).

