## Methods

### Design

We follow an effectiveness-implementation hybrid design type 2, as proposed by Curran et al. [14], which allows us to simultaneously test the implementation strategy and impact of the integrated palliative care intervention on health outcomes. To study effectiveness, a cluster randomized controlled trial will be performed in eight hospital regions in the Netherlands. Furthermore, the implementation process will be evaluated using mixed methods. Each hospital region will serve as a cluster. Randomization on this cluster level instead of one-to-one randomization was chosen to reduce contamination: it is likely that professionals exposed to the implementation strategy also would treat patients assigned to the control condition differently [15].

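### The total of 347 appears to use a design effect for 30 patients per region although 44 are recruited; by the plan's own method, power for 9 points is about 77 to 78%, not 80%

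*Protocol article*

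**What the plan says.** All of the inputs stand in the section "Sample size calculation" of the protocol article, except the number of regions.

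- Target difference: the authors "used the 5% midrange bound, which equals 9 points on the FACIT-Pal".
- Spread: "Assuming a standard deviation of 25".
- Unadjusted size: "at least 121 patients per group are required to obtain a power of 80% (two-sided t-test, alpha = 0.05").
- Clustering: "a previous study found an ICC = 0.01".
- Final size: "to allow for an additional loss to follow up of 10% a total of 347 patients are needed (44 patients per region").
- Number of regions, from the section "Design": "a cluster randomized controlled trial will be performed in eight hospital regions in the Netherlands".

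The article prints neither the cluster size nor the design effect behind the step from 121 per group to 347 in total.

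**The concern.** In a cluster trial the design effect depends on how many patients are analysed in each cluster. When the number of clusters is fixed, every inflation of the total makes the clusters larger, which raises the design effect again. The required size therefore has to be solved with the final cluster size, not with the size before inflation. The printed total looks as if this was not done: it matches a design effect for 30 per region, while the same sentence plans 44.

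At stake is the power statement for the primary outcome, FACIT-Pal at 6 months. If the stated inputs do not give 80%, a reader of a null result would judge it against a power that the trial did not have.

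**Working it through.** **Inputs.** Difference 9, SD 25, two-sided alpha 0.05, power 80%, ICC 0.01, loss 10%, eight regions, 347 enrolled or 44 per region (8 x 44 = 352). I assume four regions per arm. The article does not state the ratio, but it gives one size for each group.

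**Step 1: unadjusted size.** n per group = 2 x (1.96 + 0.8416)^2 x 25^2 / 9^2 = 121.1. This agrees with the stated 121, or 242 in total.

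**Step 2: reproducing 347.** Total = 242 x [1 + (m - 1) x 0.01] / 0.9, where m is the number of patients per region.

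| m used | Design effect | Total enrolled |
|---|---|---|
| 30 (about 242/8) | 1.29 | 312.2 / 0.9 = 346.9 |
| 39 | 1.38 | 334.0 / 0.9 = 371.1 |
| 44 | 1.43 | 346.1 / 0.9 = 384.5 |

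Only the first row gives 347. Close variants that also apply both adjustments use m of 30 to 31 (for example, m = 31 with loss applied as x 1.1 gives 346.1). One other route comes near: m = 44 without any inflation for loss gives 242 x 1.43 = 346.1.

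**Step 3: power of the plan as printed.** Standard error = 25 x sqrt(4 x DE / N), with N the number analysed and DE the design effect. Power is by the normal approximation.

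| | 347 enrolled | 352 enrolled |
|---|---|---|
| Analysed (x 0.9) | 312.3 | 316.8 |
| Analysed per region | 39.0 | 39.6 |
| Design effect | 1.380 | 1.386 |
| Effective n per arm (N/2/DE) | 113.1 | 114.3 |
| Standard error | 3.32 | 3.31 |
| 9 / standard error | 2.71 | 2.72 |
| Power for 9 points | 77.3% | 77.7% |
| Difference detectable with 80% power (2.80 x SE) | 9.3 | 9.3 |

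The plan needs 121 effective patients per arm and has 113 to 114.

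**Step 4: the size that is consistent with eight regions.** Solve 4m = 121 x [1 + (m - 1) x 0.01]. This gives m = 121 x 0.99 / (4 - 1.21) = 42.9 analysed per region. Dividing by 0.9 gives 47.7 recruited per region, so 382 in total, or 384 at 48 per region. The 371 in step 2 is not a solution, because enrolling 371 would again put more than 39 analysed patients in each region.

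**Step 5: sensitivity, not the plan's method.** If the arm contrast is tested on 8 - 2 = 6 between-region degrees of freedom, the noncentral t distribution gives 62% power for 9 points at both totals. The detectable difference is about 11 points (11.2 at 347, 11.1 at 352).

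**Step 6: other ICC values (assumed; the article gives only 0.01).** At 347 enrolled, normal-approximation power is 83% at ICC 0.005 and 67% at ICC 0.02.

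**The case against.** **The shortfall is small.** It is 2.3 to 2.7 percentage points, and the detectable difference moves only from 9 to 9.3. The target is itself rounded down: 5% of the 184-point maximum is 9.2, and at 9.2 points power is 79.0% (347) or 79.4% (352). This stands as a statement about size, and it is why the point is not a critical one. It does not make the paragraph correct, because the article states 9 points as its target and its 121 per group follows from 9.

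**The cluster size of 30 is inferred.** This also stands. It would go too far to say that 347 can come only from a cluster size of 30, since a cluster size of 44 with no allowance for loss lands on nearly the same number. That route contradicts the text, which says that 10% loss is included. It also ends in the same place: after the loss about 39 per region remain, and power is again about 77%.

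**A stronger reading is tempting: that the trial has only 62% power.** A reader might infer this from the eight regions. The article does not support it as the trial's power. The section on the analysis of the effect evaluation names multilevel mixed models but no method for the degrees of freedom, and an article may leave that to the full protocol or the SAP. The 62% holds if 6 degrees of freedom are used, so it is a sensitivity result about few clusters and separate from the inconsistent cluster size.

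**Conclusion.** The point holds in a limited form. Under the plan's own inputs and method, 347 enrolled patients in eight regions give about 77% power for 9 points, and 352 give about 78%. The stated 80% corresponds to a detectable difference of about 9.3 points. About 35 more patients (382 against 347, some 10%) would be needed to reach 80% by the same method.

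The shortfall rests on equal allocation of regions, equal region sizes, 10% loss spread evenly and ICC 0.01. It does not depend on which route the authors took to 347. The documents do not support calling the trial severely underpowered on this ground: the larger loss appears only with the 6-degree-of-freedom reference or with a higher ICC, and the article states neither. The paragraph should be corrected, but the error does not threaten the trial.

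**What to change.** Keep the recruitment target of 347 (or 352 at 44 per region) and correct the paragraph:

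1. State the cluster size and the design effect: about 39 analysed per region, design effect 1.38 (39.6 and 1.39 at 352 enrolled).
2. Replace the 80% claim with about 77 to 78% power for 9 points, and give the detectable difference of about 9.3 points.
3. Add, labelled as sensitivity, that a test on 6 between-region degrees of freedom would have about 62% power and a detectable difference of about 11 points.
4. If power at other ICC values is shown, mark those values as assumed.

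This costs one reworded paragraph, a slightly less favourable power statement and no patients. If the sponsor prefers to keep 80% by the stated method, the consistent target is 48 per region, about 382 to 384 in total. That costs 35 to 37 patients more than 347. With 6 degrees of freedom this larger total would still give only about 65% power, so the paragraph should say which reference its figure uses.

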**Methods:**

An integrated palliative care intervention was developed based on existing guidelines, a literature review, and input from patient and professional organizations. To facilitate uptake of the intervention, a multifaceted implementation strategy was developed, comprising a toolbox, (communication) training, collaboration support, action planning and monitoring. Using a hybrid effectiveness-implementation type 2 design, this study aims to simultaneously evaluate the implementation process and effects on patient, informal caregiver and professional outcomes. In a cluster randomized controlled trial, eight hospital regions will be randomized to receive the integrated palliative care approach or to provide care as usual. Eligible patients are identified during hospitalization for an exacerbation using the Propal-COPD tool. The primary outcome is quality of life (FACIT-Pal) at 6 months. Secondary outcome measures include spiritual well-being, anxiety and depression, unplanned healthcare use, informal caregiver burden and healthcare professional’s self-efficacy to provide palliative care. The implementation process will be investigated by a comprehensive mixed-methods evaluation assessing the following implementation constructs: context, reach, dose delivered, dose received, fidelity, implementation level, recruitment, maintenance and acceptability. Furthermore, determinants to implementation will be investigated using the Consolidated Framework for Implementation Research.

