## Background

Chronic Obstructive Pulmonary Disease (COPD) is a common illness characterized by persistent respiratory symptoms and airflow limitation [1]. When the disease progresses, many patients experience recurrent acute exacerbations, often requiring hospital admissions with a mortality rate of up to 23% within 1 year after admission [2]. COPD is the third leading cause of death in the world [3]. Moreover, in advanced stages of the disease, patients suffer from multiple symptoms, which are frequently undertreated [4]. Accordingly, their health-related quality of life is comparable to, or even worse than that of patients with advanced lung cancer [5]. Thus, patients with COPD have at least a similar need for palliative care.

In line with the WHO definition, palliative care should not be restricted to reactive care in the terminal phase of the disease [6]. Instead, it should be provided proactively and earlier in the course of the disease, complementing disease-modifying care. Its goal is to enhance quality of life through assessment and treatment of physical, psychological, social and spiritual problems. Additionally, it is advocated that palliative care should take into account the maintenance of the patient’s autonomy, access to information and treatment options [7], which requires ongoing communication including advance care planning and care coordination. In accordance with current recommendations, palliative care provision should principally be provided by generalist care professionals, i.e. general practitioners and respiratory care specialists in the case of COPD-care, whereas patients can be referred to specialist palliative care if needed [7, 8]. Consequently, palliative care should be an integrated part of regular COPD-care, in which professionals collaborate in multidisciplinary teams to optimize continuity of care.

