#### Patients

Patients diagnosed with COPD and admitted to the hospital for an acute exacerbation will be invited to participate in the study. Patients not able to complete questionnaires in Dutch, patients with severe cognitive decline (e.g. dementia) and patients on the waiting list for lung transplantation will be excluded. After completion of the baseline questionnaire, patients will be screened using the Propal-COPD tool [16]. Patients with a positive Propal-COPD score will be included in the effectiveness study. The Propal-COPD tool consists of seven indicators: Medical Research Council (MRC) dyspnea score of 5, Clinical COPD Questionnaire (CCQ) score > 3, forced expiratory volume in 1 s lower than 30% predicted, presence of specific comorbidities, body-mass index lower than 21 kg/m2 or weight loss (> 10% in the last 6 months or > 5% in last month), previous hospitalization for acute exacerbation in the last 2 years (last 2 years ≥2 admissions or last year ≥1 admission), and a negative answer to the surprise question (“Will you be surprised if your patient would die in the next coming 12 months?”) [16]. For each indicator, specific weight is given, together generating a total score. A score exceeding the previous published cut off value of − 1.362 corresponds with a high probability for death within 1 year, which is considered a proxy for having palliative care needs.

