### Intervention

Table 1 details the components of the integrated palliative care approach, consisting of an integrated palliative care intervention and an multifaceted implementation strategy. Figure 1 shows the causal assumptions of its outcomes and mechanisms of impact, based on the Medical Research Council framework [26]. The integrated palliative care intervention developed follows existing palliative care guidelines [27, 28], the Quality Framework Palliative care of the Netherlands [29], a literature review and input from the expert groups. For the identification of patients that are likely to benefit from palliative care, the previously validated Propal-COPD tool will be used. This tool has been validated in patients admitted to the hospital for acute exacerbation and showed to have a high sensitivity of 90% and specificity of 73% [16]. Moreover, admission for an acute exacerbation of COPD is considered to be one of the key milestones for transition towards a palliative approach [30] and seems to be a feasible moment to start proactive palliative care [31, 32]. After identification, one or more consultations take place either in the outpatient clinic or in the general practice, depending on the patient’s needs, for a multidimensional assessment, symptom management and advance care planning. The treatment plan and agreements made will be documented and shared with other involved professionals and discussed in a multidisciplinary meeting if needed. In case of preference for care at home, the responsibility will be transferred to the patient’s general practitioner. If a patient deceases, the provided end-of-life care will be evaluated with the patient’s informal caregiver and involved healthcare professionals.

**Table 1 Tab1:** Description of the implementation strategy and integrated palliative care intervention of the Compassion study

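### The 10% loss allowance leaves no room for deaths before the 6-month endpoint and looks too low against the protocol's own mortality and Propal-COPD figures, so the 80% power is not supported

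*Protocol article*

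**What the plan says.** The abstract fixes the endpoint: "The primary outcome is quality of life (FACIT-Pal) at 6 months". The section Sample size calculation takes a difference of 5% of the scale, "which equals 9 points on the FACIT-Pal", and continues "Assuming a standard deviation of 25". This leads to 121 patients per group for 80% power. Clustering (ICC 0.01) and one loss term, "to allow for an additional loss to follow up of 10" per cent, bring the total to 347, or 44 per region. Death is not mentioned in that section.

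Three other places bear on the loss term:
- The Background describes "hospital admissions with a mortality rate of up to 23% within 1 year after admission".
- The section Patients includes in the effectiveness study only patients above a Propal-COPD cut-off that "corresponds with a high probability for death within 1 year".
- The section Intervention reports that the tool, validated in patients admitted for an acute exacerbation, "showed to have a high sensitivity of 90% and specificity of 73" (per cent).

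**The concern.** A patient who dies before 6 months cannot complete the 6-month FACIT-Pal. Selecting patients for a high risk of death within a year therefore makes death a predictable and possibly large source of missing primary outcomes. Questionnaire non-response among severely ill survivors comes on top. If 10% has to cover both, the number of patients with a 6-month score will fall below what the calculation assumes. The trial would then have less power than stated, and a null result could be read as stronger evidence against the intervention than it is.

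**Working it through.** **Inputs.** From the protocol: difference 9, SD 25, two-sided alpha 0.05, power 80%, ICC 0.01, 8 regions, loss 10%, one-year mortality up to 23%, sensitivity 0.90, specificity 0.73. Assumed here: constant hazard over the year, and tool accuracy in this trial equal to the reported accuracy.

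**1. Reproduce the plan's total.**
- Per group: 2 × (2.8016 × 25 / 9)² = 121.1 (normal approximation), matching 121. Two groups make 242.
- Design effect: 1 + (242/8 − 1) × 0.01 = 1.2925.
- Total: 242 × 1.2925 / 0.90 = 312.8 / 0.90 = 347.5, matching 347.

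Nothing is left over, so no separate death allowance is hidden in the total.

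**2. Mortality among Propal-positive patients.** Let p be one-year mortality in all admitted patients. One-year mortality among positives is PPV = 0.90p / [0.90p + 0.27(1 − p)]. Six-month mortality at constant hazard is 1 − √(1 − PPV).
- p = 0.23 (protocol ceiling): PPV = 0.207 / (0.207 + 0.2079) = 0.499; by 6 months 1 − √0.501 = 29.2%. Simple halving of the one-year risk gives 24.9%.
- p = 0.10 (assumed, not in the protocol): PPV = 0.09 / (0.09 + 0.243) = 0.270; by 6 months 14.6%.
- Break-even: 10% dead by 6 months needs PPV = 1 − 0.90² = 0.19, which corresponds to p of about 0.066.
- No enrichment at all, p = 0.23: 1 − √0.77 = 12.3% by 6 months.

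**3. Power with 347 enrolled.** The design effect is held at the plan's 1.2925, so only the loss term changes. Effective n per arm = 347 × (1 − loss) / 2 / 1.2925. Power uses the normal approximation for 9 points and SD 25. Detectable difference at 80% power = 2.8016 × 25 × √(2 / effective n). N needed = 312.8 / (1 − loss).

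| Loss at 6 months | Analysed | Effective n per arm | Power | Detectable difference | N needed for 80% |
|---|---|---|---|---|---|
| 10% (plan) | 312 | 120.8 | 79.9% | 9.0 | 347 |
| 15% (assumed) | 295 | 114.1 | 77.6% | 9.3 | 368 |
| 20% (assumed) | 278 | 107.4 | 75.1% | 9.6 | 391 |
| 29.2% (deaths at p = 0.23) | 246 | 95.0 | 69.9% | 10.2 | 442 |
| 36.3% (29.2% dead, then 10% of survivors lost) | 221 | 85.5 | 65.3% | 10.7 | 491 |

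The last loss figure is 1 − 0.708 × 0.90 = 0.363.

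**The case against.** The strongest defence is that 10% is an optimistic input, not a mistake in the sums: the total reproduces. That is right, and the point concerns the input only.

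The 29% is also an upper end. The 23% is an up-to value for admitted patients generally. Participants must consent and complete questionnaires in hospital, and those with severe cognitive decline are excluded, so their mortality may be lower. The Discussion itself says the tool's robustness needs further testing. All of this stands. The lower rows of the table are not the protocol's figures either: 15% corresponds roughly to an assumed 10% one-year mortality that appears nowhere in the document. What survives is the break-even. Deaths alone stay within 10% only if one-year mortality in all admitted patients is about 6.6% or less, under a third of the quoted ceiling, and that leaves nothing for non-response.

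The power loss is also computed for a simple two-group comparison. FACIT-Pal is collected at baseline, 3 and 6 months, and multilevel mixed models are planned. Patients who die after 3 months may still contribute. Baseline adjustment with an assumed baseline-to-6-month correlation of 0.3 or 0.5 would give about 74% or 82% at 246 analysed. The article does not fix either feature, and the sample size calculation does not rely on them, but they could offset some or all of the shortfall.

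A reader might go further and infer that the plan treats death as ordinary loss. The article does not say so. How deaths enter the analysis may be set out in an SAP or full protocol that is not shown, and date of death is a listed secondary outcome. A reader might also infer that early death will count as low healthcare use, because Table 2 records visits and admissions "in the 12 months pre-enrollment up to 12 months after enrollment". That row describes data collection, not analysis, and nothing in it rules out accounting for time alive. Any figure for bias from unequal survival would need a mortality difference between arms that the document does not supply.

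**Conclusion.** The concern holds as a point about one design input. The 10% allowance has no stated death component and looks too low for a population selected on predicted one-year mortality. On the protocol's ceiling figures, about 29% would be dead by 6 months. Ignoring the enrichment, the same ceiling still gives about 12%. Power would be roughly 2 points below the nominal 80% at 15% loss, 10 points below at 29%, and about 15 points below if a tenth of survivors are also lost.

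The size rests on a constant hazard, on transportable tool accuracy, on how far true mortality lies below 23%, and on an analysis that gains nothing from 3-month or baseline scores. The direction is firmer than the size. The stated 80% is not supported by the protocol's own inputs.

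**What to change.** Replace the single 10% with two components: deaths before 6 months among Propal-positive patients, and non-response among survivors. Present them as a range, mark which values come from the protocol and which are assumed, and state the hazard and tool-accuracy assumptions. Then restate power and detectable difference at the resulting analysable numbers instead of keeping the 80% claim. If the design counts on repeated measures or baseline adjustment to recover power, say so and give the assumed correlation.

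This costs a paragraph and a small table, and a less favourable headline power. Holding 80% by recruitment instead would, by the plan's own method, take about 368 patients at 15% loss and 442 at 29%.

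Optional and secondary: since dates of death are collected, unplanned care can be analysed per time alive, at little extra work.
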